## Methods

### Study Design

This is a quantitative longitudinal study with data collected from subscribers of the Wellness4MDs program using a web-based survey at the onset of the program and at designated follow-up timepoints. The surveys will include questions related to sociodemographic characteristics, roles, years of training, specialty, work, and clinical information. The Wellness4MDs program will deliver daily supportive and informative SMS text messages with or without embedded web links for mental health support or literacy resources to subscriber cell phones for 6 months. Participation in the surveys would be voluntary, and nonparticipation in any of the surveys will not impact program participation or service delivery. The Wellness4MDs is a national collaborative project that will leverage stakeholder partnerships to disseminate the program to physicians, postgraduate trainees, and medical students. Potential collaborating organizations include the Royal College of Physicians and Surgeons of Canada, faculties of medicine across Canada, provincial medical associations, provincial health authorities, and provincial medical licensing colleges. Initially, promotional material will be provided and give an overview of the Wellness4MDs program and information about how physicians, postgraduate medical trainees, and medical students can subscribe and unsubscribe to the program. Collaborating organizations will be requested to share information about the Wellness4MDs program with physicians, postgraduate medical trainees, and medical students on their databases and social medical handles, including Facebook, LinkedIn, Instagram, and Twitter (rebranded as X). Thus, the Wellness4MDs recruitment plan will mirror the successful recruitment plan of similar programs in Alberta, including the Text4Hope program that was launched in response to COVID-19 in March 2020 [36,37,43] as a collaborative initiative between the University of Alberta, Alberta Health Services, and six health foundations. Text4Hope was the subject of a wide-exposure communications campaign (television, radio, internet, and print media), including the local provincial mental health foundation, Alberta Health Services, and a media release by the provincial chief medical officer [44].

### Study Setting and Participants

The bilingual Wellness4MDs program will enroll physicians, postgraduate trainees, and medical students in all provinces and territories in Canada. In 2021, the total number of physicians in Canada was 108,040, according to the annual census [45]. According to the Canadian Medical Association, the total number of residents in all postgraduate programs in 2018-2019 was 16,508, and the total enrollment in undergraduate medical schools in Canada in 2017-2018 was 11,737 [46].

### Program Timelines

The Wellness4MDs initiative will be a 3-year project, with timelines as detailed in Table 1.

**Table 1 table1:** Wellness4MDs project Gantt chart.

Milestones			Year 1									Year 2									Year 3						
			Q1^a^		Q2^b^		Q3^c^		Q4^d^		Q1			Q2		Q3		Q4		Q1			Q2		Q3		Q4
**Milestone 1: recruitment of a project staff and creation of the bank of supportive SMS text messages**																											
	1.1 A project coordinator and evaluation specialist would be recruited to support project coordination, implementation, monitoring, and evaluation	✓																									
	1.2 Review and adaptation of the bank of supportive SMS text messages and creation of new messages for the Wellness4MDs program by an expert group	✓																									
**Milestone 2: launch of the Wellness4MDs program, advertisement, and delivery of service**																											
	2.1 Recruitment			✓		✓		✓		✓			✓		✓		✓		✓			✓					
	2.2 Provision of the service			✓		✓		✓		✓			✓		✓		✓		✓			✓		✓		✓	
**Milestone 3: evaluation of the service, including clinical assessment and satisfaction of the participants, and stakeholders’ feedbacks**																											
	3.1 Baseline survey (excluding satisfaction survey)			✓		✓		✓		✓			✓		✓		✓		✓			✓		✓		✓	
	3.2 Follow-up survey (including satisfaction survey)					✓		✓		✓			✓		✓		✓		✓			✓		✓		✓	
	3.3 Key informant interviews and Focus group workshops												✓									✓					
**Milestone 4: data compilation, analysis, and preparation of reports, publications, and presentations for multi-scale dissemination**																											
	4.1 Data compilation							✓		✓			✓		✓		✓		✓			✓		✓		✓	
	4.2 Data analysis							✓		✓			✓		✓		✓		✓			✓		✓		✓	
	4.3 Preparation of reports, publications, and presentations							✓		✓			✓		✓		✓		✓			✓		✓		✓	

^a^Q1: first quarter.

^b^Q2: second quarter.

^c^Q3: third quarter.

^d^Q4: fourth quarter.

### Wellness4MDs Program

The Wellness4MDs program is modeled on the highly successful Text4Hope and Wellness4Teachers initiatives in Canada [35,47]. The program is powered by the ResilienceNHope software, a web-based application that delivers the suite of supportive SMS text and email messaging programs, including Text4Mood, Text4Hope, Wellness4Teachers, Text4PTSI, Text4Wellness, and MoreGoodDays [48]. Canadian physicians, postgraduate trainees, and medical students will be able to subscribe to the Wellness4MDs program by texting “WellMD” to a designated phone number. Individuals can unsubscribe to the program by simply texting “stop” to the program phone number. The Wellness4MDs program will deliver daily supportive and informative SMS text messages (some with embedded web links for mental health support or literacy resources) to subscriber cell phones for 6 months. The Wellness4MDs program SMS text messages are based on CBT principles and were developed by psychiatrists, mental health therapists, clinical psychologists, and users of mental health services. About a third of the SMS text messages will have embedded web links that include additional physician health and wellness resources from reputable sources.

### Examples of SMS Text Messages

The following are example SMS text messages that will be sent.

“Perfectionism can cause anxiety. Remember a perfect work environment does not exist. Try deliberately being imperfect and see what happens. Do your anxious thoughts come true? Remember that there are many possibilities in life. Try not to limit yourself from enjoying all that is possible.” In addition, an embedded web link has been provided [49].“We each have different signature strengths. It’s not about competing with others but learning our unique strengths. Strengths come in many varieties, such as humor, curiosity, persistence, kindness, love, forgiveness, cooperativeness, and optimism. Share your strength with others. Help a struggling colleague.”“Problems are almost never solved in one step. See if you can break the problem into steps. Take the first step today by starting with a manageable situation. Get the support of a friend, family, colleagues, or supervisor.” In addition, an embedded web link has been provided [50].

### Hypothesis

We hypothesize that the Wellness4MDs program will achieve (1) at least a 20% reduction in mean scores for burnout, anxiety, and depressive symptoms on validated scales and a 20% increase in self-reported well-being at 6 weeks, 3 months, and 6 months after receiving the service, and (2) at least 80% of subscribers will express satisfaction with the program and perceive the daily supportive SMS text messages as contributing to their overall mental well-being.

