**Methods:**

This longitudinal study represents a multistakeholder, mixed methods, multiyear implementation science project. Project evaluation will be conducted through a quantitative prospective longitudinal approach using a paired sample comparison, a naturalistic cross-sectional controlled design, and satisfaction surveys. Prevalence estimates for psychological problems would be based on baseline data from self-completed validated rating scales. Additional data will be collected at designated time points for paired comparison. Outcome measures will be assessed using standardized rating scales, including the Maslach Burnout Inventory for burnout symptoms, the 9-item Patient Health Questionnaire for depression symptoms, the 7-item Generalized Anxiety Disorder scale for anxiety symptoms, and the World Health Organization–Five Well-Being Index.

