### Sample Size Calculation

With a projection that the effect size for the reduction in mean 7-item Generalized Anxiety Disorder (GAD-7) scale and 9-item Patient Health Questionnaire (PHQ-9) scores at 6 months from baseline would be 0.1, a population variance of 1 for each scale mean score, a 2-sided significance level α=.05, and a power of 90% (β=.1), using a web-based script [51], we estimated that the sample size needed to assess the effects of the daily supportive SMS text messages on the outcome variables would be 1053.

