### Statistical Analysis

Quantitative data will be analyzed with descriptive statistics, paired *t* test, and chi-square tests using SPSS Statistics for Windows (Version 25; IBM Corp) [64]. Descriptive data will be presented as numbers and percentages. Paired *t* test will be used to assess the differences in the mean scores of each of the outcome scales for the baseline and the follow-up time points. In addition, the chi-square test will be used to compare the prevalence of burnout, likely GAD and likely MDD, from baseline to the follow-up time points.

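### Hypothesis 1 claims at least a 20% change, but the stated test for mean scores is against zero and the sample size is for 0.1 SD, so a significant result does not show 20%

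*Protocol article*

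**What the plan says.** Three sections of the protocol article bear on this point.

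- **Hypothesis.** The first hypothesis sets a threshold for the symptom scales: "at least a 20% reduction in mean scores for burnout, anxiety, and depressive symptoms on validated scales". It also expects WHO-5 scores to rise by the same percentage at all three follow-up times.
- **Sample Size Calculation.** The effect size for the fall in mean GAD-7 and PHQ-9 "scores at 6 months from baseline would be 0.1, a population variance of 1 for each scale mean score". With "a 2-sided significance level α=.05" and 90% power, the number needed to assess effects "on the outcome variables would be 1053". The section does not mention 20%, and it covers two of the four primary scales at one of the three follow-up times.
- **Statistical Analysis.** For mean scores, a paired t test "will be used to assess the differences in the mean scores of each of the outcome scales" at baseline and follow-up. No non-zero null value, confidence-bound rule or success criterion is given. Chi-square tests are planned for the prevalence outcomes, which are secondary.

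The abstract describes the evaluation as a "quantitative prospective longitudinal approach using a paired sample comparison", which fits the one-sample form of the sample size.

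**The concern.** Hypothesis 1 is worded as a threshold. A paired t test with no stated null value asks a different question: whether the mean change differs from zero. The sample size is set for a third quantity, 0.1 SD, which equals a 20% change only under a particular relation between the SD of change and the baseline mean. The plan therefore names three targets and does not connect them.

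What is at stake is the reading of the lead hypothesis on all four primary outcomes (PHQ-9, GAD-7, MBI, WHO-5). With about a thousand pairs, a small change is significant. Followed as written, the plan yields a p value that does not answer hypothesis 1, and it does not say how uncertainty around an observed percent change is to be weighed against 20%.

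**Working it through.** **Inputs from the article.** Effect 0.1 with variance 1, two-sided alpha .05, power 90%, n = 1053, paired comparison, hypothesised change 20%.

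**Inputs not in the article.** Baseline means, SDs, SDs of change and pre-post correlations. These are assumed below, with ranges.

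**1. Reproducing 1053.** For a paired (one-sample) mean:

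- Normal approximation: n = ((1.960 + 1.282)/0.1)² = 1050.7, so 1051.
- Adding the small-sample term 1.960²/2 = 1.92: 1052.7, so 1053.
- Noncentral t: power is 0.8998 at 1052 and 0.9001 at 1053, so exactly 1053.

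The figure is right for a paired t test against zero. A two-sample calculation would give 2102 per group, and a one-sided one 857.

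**2. Smallest significant change at n = 1053.**

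t(0.975; 1052)/√1053 = 1.962/32.45 = 0.0605 SD of the paired differences.

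**3. The same change as a percentage.** Let R = SD of the differences / baseline mean. Then:

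- significance threshold = 6.05% × R
- design effect (0.1 SD) = 10% × R
- a 20% change in SD units = 0.20/R

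| Assumed R | Threshold | Design effect | 20% in SD units | Pairs for 90% power against zero at a true 20% |
|---|---|---|---|---|
| 0.5 | 3.0% | 5% | 0.40 | 68 |
| 0.7 | 4.2% | 7% | 0.29 | 131 |
| 0.8 | 4.8% | 8% | 0.25 | 171 |
| 1.0 | 6.0% | 10% | 0.20 | 265 |
| 1.2 | 7.3% | 12% | 0.17 | 381 |

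Assume PHQ-9 or GAD-7 baseline means of 5 to 10 and SDs of change of 4.5 to 6. R then runs from 4.5/10 = 0.45 to 6/5 = 1.2, which gives:

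- threshold: 6.05% × 0.45 = 2.7% to 6.05% × 1.2 = 7.3%
- design effect: 4.5% to 12%
- a 20% change: 0.20/1.2 = 0.17 to 0.20/0.45 = 0.44 SD, or 1.7 to 4.4 times the planning effect

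Wider assumptions (means 5 to 10, score SDs 4 to 6, pre-post correlation 0.3 to 0.7) give a threshold of 1.9% to 8.6%.

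**4. A check that needs no particular SD.** A 20% change equals 0.1 SD only if R = 2. It equals the significance threshold only if R = 0.20/0.0605 = 3.3. A score bounded between 0 and M has SD at most √(mean × (M − mean)). Assume equal SDs at both times and a correlation of at least 0.5, so that the SD of the differences is no larger than the score SD.

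- R = 2 then requires a mean of at most M/5: 5.4 on PHQ-9 (M = 27), 4.2 on GAD-7 (M = 21), 20 on WHO-5 (M = 100).
- R = 3.3 requires a mean below about 2.3 on PHQ-9 and 1.8 on GAD-7.

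Even at those limits, scores would have to be nearly all-or-nothing. The gap is therefore not a product of the chosen SDs.

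**5. What a strict 20% rule would cost.** If the whole 95% CI had to lie beyond 20%, power would be 2.5% at a true reduction of exactly 20%. At a true 25% and n = 1053 it would be about 90% (R = 0.5) down to 37% (R = 1.0). These two figures are approximate, because they use the SD of the simple differences for the contrast with 0.8 × baseline.

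**The case against.** The strongest reply is that a hypothesis stated as an expected effect, with a test against zero, is common practice, and that a formal decision rule is often left to an analysis plan that is not shown here. On a plain reading, an observed reduction below 20% does not meet the hypothesis, and percent change follows directly from the means being compared. Planning for a smaller effect than the one expected is also conservative: the mismatch costs the planned test no power.

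Much of this stands. The absence of a rule would not be a finding by itself. What remains is that the article states a threshold, a test and a sample size that do not refer to one another. If 20% is only an expectation, the Hypothesis section should say so.

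Four stronger readings are tempting and not supported:

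- *That a specific small reduction, such as 4% to 5%, would pass.* This needs R of about 0.66 to 0.83, and the article gives nothing from which to derive R. Only 0.06 SD follows from its own figures.
- *That the sample size is wrong.* It reproduces exactly for the any-change test.
- *That the paired t test is the only test in the plan.* It is the only one stated for mean scores; chi-square tests are stated for prevalence.
- *That the plan treats p<.05 as confirming hypothesis 1.* It nowhere says so.

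For WHO-5, it is also unclear whether the words at least carry over to the 20% increase.

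**Conclusion.** The mismatch is real and affects the lead hypothesis on the primary outcomes. The stated test for mean scores addresses any change. At 1053 pairs it is significant from an observed 0.06 SD of the paired differences, so a significant result would not show a 20% change. In percent terms the threshold is about 2.7% to 7.3% of the baseline mean if means are 5 to 10 and SDs of change 4.5 to 6, and about 2% to 9% over the wider range. These percentages rest on assumed values for PHQ-9 and GAD-7. No comparable range is offered for the MBI or WHO-5, although the rule 6.05% × R applies to any scale with 1053 pairs.

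The conclusion does not extend to the sample size arithmetic, which is sound, or to the power of the test against zero, which is ample for a 20% change under these assumptions.

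**What to change.** Make three changes, to be fixed before analysis:

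1. For each primary scale and follow-up time, report the percent change in mean score with a 95% CI, and judge hypothesis 1 by comparing the estimate and its CI with 20%. One direct route is the mean of follow-up − 0.8 × baseline for symptom scores (below zero means a reduction of more than 20%) and follow-up − 1.2 × baseline for WHO-5 (above zero means an increase of more than 20%).
2. Report the paired t test separately, as evidence of any change.
3. State in the Sample Size Calculation section that 1053 is sized to detect any change, at 0.1 SD, and not for hypothesis 1.

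Alternatively, restate hypothesis 1 as any reduction (and any increase in well-being), with 20% as the expected size. The test and the sample size section then address the hypothesis as worded.

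**Cost.** A few sentences, with the same data. Under the first route the 20% claim becomes harder to support. Requiring the whole CI to lie beyond 20% should be optional, given 2.5% power at a true reduction of exactly 20%. If that strict rule is adopted, it needs its own sample size, because 1053 was not derived for it.

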### Sample Size Calculation

With a projection that the effect size for the reduction in mean 7-item Generalized Anxiety Disorder (GAD-7) scale and 9-item Patient Health Questionnaire (PHQ-9) scores at 6 months from baseline would be 0.1, a population variance of 1 for each scale mean score, a 2-sided significance level α=.05, and a power of 90% (β=.1), using a web-based script [51], we estimated that the sample size needed to assess the effects of the daily supportive SMS text messages on the outcome variables would be 1053.

### Data Collection and Outcome Measures

The project will run for 3 consecutive years. Quantitative data will be collected from subscribers of the Wellness4MDs program using a web-based survey at the onset of the program (baseline), 6 weeks, 3 months (midpoint), and 6 months (end of service) as illustrated in Table 2. The surveys will include demographic questions such as sex and gender, as well as information about their role (physicians, postgraduate trainees, or medical students), their years of training or practice, and their specialty of retaining or practice if they are residents or physicians, in addition to the clinical outcome measures.

Primary outcome measures include changes in the mean scores on the PHQ-9 [51], the GAD-7 [52], the Maslach Burnout Inventory (MBI) [53], and the World Health Organization-Five Well-Being Index (WHO-5) [54] for subscribers from baseline to 6 weeks, 3 months, and 6 months.

The PHQ-9 is a self-administered scale designed to measure likely depression. It is an effective tool for patients and a validated tool for screening of depressive symptoms among the general population [55]. Symptoms experienced by patients during the 2 weeks before answering questionnaires are considered. Scores range from never (0), several days (1), more than half of days (2), to 3 (nearly every day), with every item ranging from 0 to 27 [51,56]. The tool’s reliability and validity have shown good psychometric properties with accepted sensitivity using 10 or above as a cutoff score and high internal consistency (Cronbach α=0.79) [55,57].

The GAD-7 scale is a self-administered valid tool designed to measure likely anxiety [58,59]. The 7 self-reported items are used to assess the severity of generalized anxiety disorder (GAD) symptoms over the past 2 weeks. Ratings are based on a 4-point Likert scale: not at all sure (0), several days (1), over half the days (2), and nearly every day (3). The scores ranged from 0 to 21, with higher scores indicative of more severe symptoms. A sensitivity of 89% and a specificity of 82% for a cutoff score of 10 [59] are considered. The GAD-7 also showed good test-retest reliability (intraclass correlation 0.83), as well as excellent internal consistency (Cronbach α=0.92) [58,60].

The WHO-5 is a self-reported measure of subjective well-being that is highly useful in clinical practice and in research studies to assess well-being over time or to compare well-being between groups [61]. The scale includes 5 positively worded items with a 6-point Likert scale used to assess participant’s feelings in the last 2 weeks, ranging from 0 (not present) to 5 (constantly present). The raw scores are transformed into a score from 0 (worst thinkable well-being) to 100 (best thinkable well-being) [62]. Having a score <50 indicates poor emotional well-being and requires further evaluation. The WHO-5 demonstrated satisfactory internal consistency reliability and concurrent validity with other scales [61,62].

**Table 2 table2:** Client-oriented outcome measures and feedbacks and experiences of clients and stakeholders.

Construct	Tool (scale)	T_0_^a^	T_1_ ^b^	T_2_ ^c^	T_3_ ^d^
Likely MDD^e^	PHQ-9^f^	✓	✓	✓	✓
Likely GAD^g^	GAD-7^h^	✓	✓	✓	✓
Burnout	Maslach Burnout Inventory	✓	✓	✓	✓
Mental well-being	WHO-5^i^	✓	✓	✓	✓
Satisfaction with the service	Standardized satisfaction survey		✓	✓	✓
Experience and feedback	Focus groups and key informant interviews				✓

^a^T_0_: baseline timepoint.

^b^T_1_: 6-week timepoint.

^c^T_2_: 3-month timepoint.

^d^T_3_: 6-month timepoint.

^e^MDD: major depressive disorder.

^f^PHQ-9: 9-item Patient Health Questionnaire.

^g^GAD: generalized anxiety disorder.

^h^GAD-7: 7-item Generalized Anxiety Disorder.

^i^WHO-5: World Health Organization-Five Well-Being Index.

The MBI, a short questionnaire-based tool, is designed to measure the symptoms and severity of burnout. In total, 3 main domains are examined, that are depersonalization, emotional exhaustion, and professional fulfillment index. The professional fulfillment index includes 2 domains, that are work exhaustion and interpersonal disengagement (Burnout scale) and the professional fulfillment scale. The reliability of MBI is supported by several studies, where Cronbach α ratings of 0.90 for emotional exhaustion, 0.76 for depersonalization, and 0.76 for personal accomplishment [63].

Secondary outcome measures include changes in prevalence in subscribers of burnout, likely GAD and likely major depressive disorder (MDD), from baseline to 6 weeks, 3 months, and 6 months measured using the GAD-7, the PHQ-9, and the MBI. Other secondary outcome measures include subscriber satisfaction.

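### Four scales at three follow-ups are all primary, with no primary time point or success rule, while the .05 level and the 90% power describe a single test

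*Protocol article*

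**What the plan says.** All references are to the Protocol article.

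- **Data Collection and Outcome Measures.** "Primary outcome measures include changes in the mean scores on the PHQ-9", and also on the GAD-7, the MBI and the WHO-5, "for subscribers from baseline to 6 weeks, 3 months, and 6 months". No scale and no visit is ranked above the others. The same section describes three main MBI domains and defines no total score.
- **Statistical Analysis.** A paired t test compares baseline with the follow-up time points for each outcome scale.
- **Sample Size Calculation.** The sizing covers GAD-7 and PHQ-9 only. It takes an effect size for the reduction in "scores at 6 months from baseline would be 0.1", with "a population variance of 1 for each scale mean score", a two-sided .05 level and "a power of 90% (β=.1"). The result is that the number needed for the "outcome variables would be 1053".
- **Hypothesis.** At least a 20% improvement is expected on burnout, anxiety, depression and well-being at all three follow-ups. The scales and visits are joined by the word *and*, but this is not presented as a rule for declaring success.

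**The concern.** The primary endpoint and its time point are things a protocol itself settles, and here they are settled as a list of at least twelve equal comparisons. Followed as written, the plan lets any scale at any visit be reported as the primary result at .05. The sizing paragraph implies that 6 months matters most, but the outcome section does not say so, and two of the four primary scales (MBI and WHO-5) are not mentioned in the sizing at all.

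The stated operating characteristics, 5% error and 90% power, are those of one test. They do not carry over to the set of primary outcomes, whichever way success is defined. The Conclusions in the Abstract and the Limitations section both direct the findings to policy makers, so it matters which result counts as the primary one.

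**Working it through.** **Inputs from the document.** Four scales; three follow-ups; paired t test for each; two-sided .05; power 90%; effect 0.1; variance 1; sample size 1053.

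**Inputs assumed.** The document gives no correlations between scales or between visits, so a range is used. An effect of 0.1 on MBI and WHO-5 and at the earlier visits is also assumed, because the sizing gives it only for GAD-7 and PHQ-9 at 6 months.

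**1. The plan's own figure.** For a paired change, n = ((1.960 + 1.282)/0.1)² = 1050.7, so 1051 by the normal formula. The exact t calculation gives 1053. The stated number is reproduced, and it is the number of complete pairs for one test at .05.

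**2. Number of primary tests.** 4 × 3 = 12. With the MBI as three domains, 6 × 3 = 18.

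**3. If any one significant result counts.** Assume no true change on any scale at any visit, and one analysis.

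- Independent tests: 1 − 0.95¹² = 46%; for 18 tests, 1 − 0.95¹⁸ = 60%.
- Correlated tests: 400,000 multivariate normal draws, threshold 1.96. The correlation of two tests is the product of the between-scale and between-time values.

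| Between scales / between times | 12 tests |
|---|---|
| 0.3 / 0.3 | 42% |
| 0.5 / 0.5 | 36% |
| 0.7 / 0.7 | 27% |
| 0.8 / 0.8 | 21% |
| 0.9 / 0.9 | 15% |

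For 18 tests at 0.5 / 0.5 the figure is 45%.

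**4. Why 46% is only an upper bound.** The three changes on one scale share a baseline. With equal variances σ² and equal correlation r between visits, each change has variance 2σ²(1 − r), and two changes have covariance σ²(1 − r). Their correlation is therefore 0.5 whatever r is. With 0.5 between times and entirely uncorrelated scales, the simulation gives 41%.

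**5. If all must succeed.** The error is at most 5%. Power at 1053 pairs is Φ(0.1 × √1053 − 1.960) = Φ(3.245 − 1.960) = 90% for each test. For all 12 jointly:

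- independent: 0.9006¹² = 28%;
- simulated: 51% at 0.5 / 0.5 and 63% at 0.7 / 0.7.

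Even GAD-7 and PHQ-9 together at 6 months reach only 0.9006² = 81% if independent, and 85% at a correlation of 0.7.

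**6. After the fix.** With four scales at 6 months only, the unadjusted any-one error would still be 1 − 0.95⁴ = 18.5% if independent and 13% at a correlation of 0.7, so an adjustment is still needed. Power per scale at 1053 pairs for each Holm level:

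| Level | Power |
|---|---|
| .05/4 = .0125 | Φ(3.245 − 2.498) = 77% |
| .05/3 = .0167 | Φ(3.245 − 2.394) = 80% |
| .05/2 = .025 | Φ(3.245 − 2.241) = 84% |
| .05 | Φ(3.245 − 1.960) = 90% |

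For 90% power at .0125, n = ((2.498 + 1.282)/0.1)², which is about 1429.

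**The case against.** The strongest reply is the Hypothesis section. It is the document's only statement of what success looks like, and it joins every scale and every visit. Read as a requirement that all succeed, it leaves no inflation. It also sets a 20% threshold, so a bare p < .05 on one scale would not satisfy it. This has weight: the any-one percentages are conditional on a rule the document does not adopt. But the document does not adopt the all-required rule either. The planned t tests assess any difference rather than a 20% one, and under the all-required reading the 90% power no longer describes the claim.

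A second reply is that multiplicity procedures are often left to an analysis plan, and this is a condensed article. That is fair as to the procedure. It does not cover the endpoint structure, which the article itself states as equal primaries.

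Three stronger readings are tempting and are not supported:

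- **That the plan has a 46% false-positive rate.** This needs independent tests, which a shared baseline rules out. Every figure here depends on assumed correlations.
- **That the plan breaks a promised 5% family-wise rate.** No such rate is claimed; .05 is an input to a single-test sample size.
- **That repeated quarterly testing adds to the error.** Table 1 ticks "4.2 Data analysis" in nine successive quarters, but it mentions no interim significance tests, early claims or stopping. The entries may be descriptive reporting. They play no part in the figures above.

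**Conclusion.** The point stands in a limited form. The article fixes at least 12 primary comparisons of equal rank, and it names neither a primary time point nor a success rule.

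- Under an any-one rule, with no true change on any outcome and a single analysis, the chance of a false primary result is about 27% to 42% for correlations of 0.7 to 0.3. It falls to 15% at 0.9, which is still three times the nominal level.
- Under an all-required rule, error is controlled, but joint power is well below 90% across the correlations examined.

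The sample size of 1053 is correct for the single test it describes. The defect is that neither the 5% nor the 90% applies to the primary outcomes as listed.

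**What to change.** 1. Under Data Collection and Outcome Measures, name change from baseline to 6 months as primary, since the sizing already uses it, and move 6 weeks and 3 months to secondary.
2. Apply Holm across the four scales at 6 months, with one named MBI subscale. Alternatively, state that all four must succeed and restate the joint power. With four scales at .05 this is 0.9006⁴ = 66% if independent, and higher with positive correlation.
3. Under Sample Size Calculation, state the power at the strictest Holm step: 77% at .0125 with 1053 pairs. If 90% is wanted at that step, about 1429 pairs are needed. Say that the effect of 0.1 is also assumed for MBI and WHO-5.
4. Optionally, add one sentence that the confirmatory analysis is the one after the last 6-month survey.

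The cost is a few sentences. The downside is a less favourable stated power, and results at 6 weeks and 3 months could no longer be presented as primary.
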